#### Visit 3 (day 0)

#### This visit will occur one week after baseline. At this visit, subjects will receive study medication for 1 month and be instructed on the dose.

#### Visit 4 (week 2)

At this visit subjects will be screened for worsening of depression (>30 on the BDI) and suicidal ideation using question #9 from the BDI. If either of these occurs the subject will be immediately referred for standard care and will be exited from the study. General health adverse events will also be recorded at this visit. [name] will be available by pager 24 hours a day to address patient safety issues. [name] will be available to discuss these cases with [name]. The subject will be instructed to bring their medication bottle to their next scheduled visit.

Visit 5 (week 4)

All measures except PE/neurological exam/EDSS, the Food Frequency questionnaire, and the MSFC will be assessed at this visit. A research assistant will draw blood for prothrombin time (PT/INR), comprehensive metabolic panel, cytokine levels, and RBC fatty acid analysis. A research assistant will assess the subject for adverse events and perform a pill count. The subject will also be asked about any changes in medication or doses of medications (prescribed and over the counter). The subject will be instructed to bring their medication bottle to their next scheduled visit.

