#### Visit 6 (week 8)

MADRS and BDI will be administered. A research assistant will assess the subject for adverse events and perform a pill count. The subject will also be asked about any changes in medication

or doses of medications (prescribed and over the counter). The subject will be instructed to bring their medication bottle to their next scheduled visit.

Visit 7 (week 12)

This visit will assess all of the same measures as Visit 2. In addition, the subject will return all remaining study drug and a pill count will be performed. If the subject has achieved a 50% improvement on their BDI or MADRS score they may choose to continue on in the study for another 3 months or to exit the study. If the subject chooses to remain in the study, we will review the consent form for Phase II of the study and attain consent before proceeding with Phase II. After being consented the subject for the subject will receive another month’s supply of study medication and will be instructed to bring this bottle to their next scheduled visit.

Table 1. Study Schedule: Phase I

| **Assessments** | **Visit 1**  Screen | **Visit 2**  Baseline | **Visit 3**  Wk 0 | Phone  Wk 1 | **Visit 4**  Wk 2 | Phone  Wk 3 | **Visit 5**  Wk 4 | **Visit 6**  Wk 8 | Phone  Wk 10 | **Visit 7**  Wk 12 |
| --- | --- | --- | --- | --- | --- | --- | --- | --- | --- | --- |
| Family and Medical Hx | X |  |  |  |  |  |  |  |  |  |
| PE/Neurological exam/EDSS |  | X |  |  |  |  |  |  |  | X |
| SCID | X |  |  |  |  |  |  |  |  |  |
| BDI | X | X |  | X | X | X | X | X | X | X |
| MADRS | X | X |  |  |  |  | X | X |  | X |
| MMSE | X |  |  |  |  |  |  |  |  |  |
| MSQLI |  | X |  |  |  |  | X |  |  | X |
| MSFC |  | X |  |  |  |  |  |  |  | X |
| Cytokine measurement |  | X |  |  |  |  | X |  |  | X |
| Metabolic panel, PT time |  | X |  |  |  |  | X |  |  | X |
| RBC fatty acid |  | X |  |  |  |  | X |  |  | X |
| Food freq. survey |  | X |  |  |  |  |  |  |  | X |
| Concomitant medications | X | X |  |  |  |  | X | X |  | X |
| Adverse Events |  |  | X | X | X | X | X | X | X | X |
| Pill Count |  |  |  |  |  |  | X | X |  | X |
| Blinding evaluation |  |  |  |  |  |  |  |  |  | X |

Table 2. Study Schedule: Phase II

| **Assessments** | Month 4 | | Month 5 | | Month 6 | |
| --- | --- | --- | --- | --- | --- | --- |
| Phone  wk  14 | Visit 8 wk  16 | phone  wk  18 | Visit 9 wk  20 | phone  wk  22 | Visit 10 wk  24 |
| Family and Medical History |  |  |  |  |  |  |

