# Product quality control

Nordic Naturals will supply the fish oil supplement. This company follows the FDA guidelines for Good Manufacturing Procedures and verifies product quality and label claim by in-house and outside lab analysis. The fish oil capsules are tested for contaminants (e.g. heavy metals), lipid oxidation, and for omega-3 fatty acid content.

Analysis of outcome variables

The major outcome measures in this study are the 3-month change in MADRS and IFN-. Initially we will compare the difference in MADRS scores, BDI scores, and IFN- levels between the fish oil and placebo groups using a two-sample t-test. In a more exploratory analysis, we will then assess whether the change in IFN- levels is correlated with the change in MADRS. To do this we will build a multiple regression model, where the predictors are the baseline MADRS or BDI and IFN- levels and the change in IFN- levels. We will additionally assess whether there is an interaction between baseline IFN- and fish oil supplementation by extending the above regression to include the interactions terms with fish oil. In order to control for potential confounders (specifically age, gender, education level, disability, and fatigue), variable selection schemes (all possible regressions using maximum R2 and backwards elimination of variable) will be used to determine if any of these potential confounders predict the dependent variable. If so, these potential confounders will be included in the regression models as covariates.

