#### Statistical Analysis Statistical power and sample size

The study that used 2g/day of E-EPA reported a 9.3-unit difference between baseline and 4-week differences in placebo and active groups for the HDRS, this difference was statistically significant (p < 0.001) [5]. The standard deviation for the groups was 7.4 (the larger of the standard deviations). A sample size of 11 subjects per group provides 80% power with an alpha= 0.05, to detect the above difference in HDRS between the treatment and placebo group. A sample size of 18 subjects per group will provide power greater than 95% with an alpha= 0.05, to detect a difference of 500 units for IFN- levels between baseline and post-treatment levels. This assumes a standard deviation of 400 units and is based on the results of a study that reported a decrease in IFN- levels in MS patients with MDD from baseline values after 16-wks of either therapy based or medication based treatments for depression [8]. Assuming a dropout rate of 20% the sample size of 60 subjects, or 30 per group is also more than adequate to detect a treatment difference in IFN- levels produced from PBMC. The additional sample will provide additional power for the exploratory analyses using the regression analysis. We are using the MADRS as the primary outcome measure as it is highly correlated with the HDRS [26-28] and will be more sensitive to treatment change in patients with MS than the HDRS. As we expect MADRS scores to have a greater change with treatment than the HDRS, we are well powered with 60 subjects.

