#### **Exclusion Criteria**

-Severe depression with suicidal ideation and plan as determined by SCID >20 and MADRS > 30

-Serious psychological disorders (e.g. psychotic disorders, bipolar disorder)

-Taking 2 or more antidepressants

-Plans to change antidepressant therapy within 3 months of enrollment

-Serious medical conditions such as congestive heart failure, cancer, liver disease, kidney failure.

-Current or past history of clinically significant ventricular arrythmias: includes patients that are receiving implantable cardioverter defibrillator (ICD) for sustained ventricular tachycardia (VT) or ventricular fibrillation (VF), or patients that had received an ICD or ICD therapy for an episode of VT/VF within the past 6 months, or subjects currently taking anti-arrythmia medications for VT/VF (e.g. Quinidine, Amiodarone).

-MS exacerbation or corticosteroid treatment 1 month prior to enrollment

-Pregnancy (pregnancy might alter results on outcome measures)

-Enrolled in another study

Because of the short duration of this study, subject participation will be stopped for the following reasons: MS exacerbation, change in MS disease modifying medication, and change or increase in antidepressant medication.

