The Data Safety and Monitoring Board of ORCCAMIND will monitor this study to ensure the safety of subjects. We will monitor adverse events by laboratory tests, which include prothrombin time (PT/INR) and comprehensive metabolic panel. For the first month of the study general health events, worsening of depression (>30 on BDI), and suicidal ideation (question # 9 on BDI) will be monitored weekly (2 x by phone and 1x in-clinic) for all subjects. If either of these occurs the subject will be immediately referred for standard care and will be exited from the study. [name] will be available by pager 24 hours a day to address patient safety issues. [name] will be available to discuss these cases with [name]. After the first month, subjects will be monitored every other week for general health events, worsening of depression (>30 on BDI), and suicidal ideation (question # 9 on BDI) (1 x by phone and 1x in-clinic). The same procedures described for month-1 will apply for all subjects throughout the study period. Subjects that have an acute MS exacerbation during the study will be referred to their neurologist for care.

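### Subjects exited for BDI above 30, suicidal ideation or an antidepressant change have no later MADRS scheduled, so some lose the week-12 primary outcome because of their depression

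*Protocol*

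**What the plan says.** Under Visit 4 (week 2), subjects are checked for a BDI above 30 and for suicidal ideation on BDI item 9, and the consequence is: "If either of these occurs the subject will be immediately referred for standard care and will be exited from the study". Section E, Protection against risk, repeats this for month 1, when subjects "will be monitored weekly (2 x by phone and 1x in-clinic) for all subjects", and then extends it: "The same procedures described for month-1 will apply for all subjects throughout the study period". The closing paragraph of the Exclusion Criteria adds further grounds: "subject participation will be stopped for the following reasons: MS exacerbation, change in MS disease modifying medication, and change or increase in antidepressant medication".

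Analysis of outcome variables sets the primary time point: "The major outcome measures in this study are the 3-month change in MADRS". Statistical power and sample size confirms the MADRS as the primary measure.

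The first post-baseline MADRS comes at Visit 5 (week 4): "All measures except PE/neurological exam/EDSS, the Food Frequency questionnaire, and the MSFC will be assessed at this visit". The next is at Visit 6 (week 8): "MADRS and BDI will be administered". The last in Phase I is at Visit 7 (week 12). Table 1 has no early-termination column. At weeks 1, 2, 3 and 10 it lists a BDI without a MADRS, and weeks 1, 3 and 10 are phone contacts.

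**The concern.** Leaving study treatment and leaving the study are treated as one event. Two of the triggers are direct signs of severe depression, and an antidepressant change may be one. A subject removed before week 12 has no primary outcome, and the reason for its absence can be the outcome itself.

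The BDI trigger is an absolute level, not a change. The Randomization section lets the moderate stratum run up to a BDI of 30, so a subject who enters at 30 exits on a one-point rise.

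If fish oil works, score-driven exits will be more frequent on placebo. Subjects who still have a week-12 MADRS will then understate the benefit. The dropout allowance ("Assuming a dropout rate of 20% the sample size of 60 subjects, or 30 per group is also more than adequate") replaces lost numbers, but it does not correct for who is lost. The trial is a pilot meant to guide a larger one, so the effect estimate matters as much as the test.

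How missing scores are analysed may be settled in a statistical analysis plan that is not shown, and it is not criticised here. The point is that the protocol stops collecting the scores, and no analysis plan can restore them.

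**Working it through.** **1. The plan's own figure.** Difference 9.3, SD 7.4, alpha 0.05 (taken as two-sided), 80% power. The standardised difference is 9.3 / 7.4 = 1.257. A two-sample t-test needs n = 10.99, so 11 per group (power 0.80), which matches the protocol. After 20% dropout, 30 × 0.8 = 24 per group remain, with power 0.989 at 9.3 units. Numbers are therefore not the problem at the planned effect.

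**2. What an exited subject leaves behind (Table 1).**

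| Exit at week | Last MADRS available | Week-12 MADRS |
|---|---|---|
| 1, 2 or 3 | baseline | none |
| 4 | week 4, if rated at that visit | none |
| 8 | week 8, if rated at that visit | none |
| 10 | week 8 | none |

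A trigger first met at week 12 loses nothing.

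**3. Size, by simulation.** The protocol gives no exit rates, so every input here is an assumption:
- 30 per arm, with baseline severity SD 5 truncated to 11-30.
- Baseline BDI mean 18, 20 or 22, which puts 18-42% in the mild stratum.
- Linear change with slope SD 7, MADRS noise SD 3.5, placebo change -4. The SD of MADRS change is √(7² + 3.5²) = 7.8.
- BDI visit noise SD 2, 3 or 4, and exit when BDI exceeds 30 at week 1, 2, 3, 4, 8 or 10.
- 6,000 trials per setting.

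With full follow-up, a t-test at a true difference of 6 has 83% power (74% with 24 per arm). In the table, the estimate and both power columns use only subjects who have a week-12 value.

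| Baseline mean | BDI noise SD | Exits, placebo vs fish oil | Estimate (true 6) | Power | Power, same losses at random | Share of exits at weeks 1-3 |
|---|---|---|---|---|---|---|
| 18 | 2 | 3.3% vs 0.9% | 5.74 | 81% | 83% | 38% |
| 20 | 2 | 5.5% vs 1.8% | 5.61 | 79% | 82% | 46% |
| 22 | 2 | 8.4% vs 3.1% | 5.51 | 77% | 80% | 52% |
| 18 | 3 | 5.5% vs 2.2% | 5.72 | 79% | 82% | 52% |
| 20 | 3 | 9.0% vs 4.0% | 5.58 | 77% | 80% | 59% |
| 22 | 3 | 13.4% vs 6.8% | 5.45 | 74% | 78% | 64% |
| 18 | 4 | 9.0% vs 4.7% | 5.70 | 78% | 81% | 61% |
| 20 | 4 | 14.0% vs 7.7% | 5.56 | 75% | 79% | 64% |
| 22 | 4 | 20.1% vs 11.8% | 5.38 | 70% | 76% | 69% |

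- Subjects lost: from 30 × (0.033 + 0.009) = 1.3 to 30 × (0.201 + 0.118) = 9.6 of 60.
- With no post-baseline MADRS: from 1.3 × 0.38 = 0.5 to 9.6 × 0.69 = 6.6.
- Between 65% and 78% of exits fall at contacts without a MADRS.
- Selection itself, beyond the lost numbers, costs 2 to 6 points of power.

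**4. Other settings.**
- True difference 9.3, means 18-22: estimate 8.6-9.0, power 97-99%.
- True difference 0: rejection rate 4.4-5.3%.
- Baseline mean 25 (only 8% mild) as an upper bound: exits 14% vs 6% to 31% vs 20%, estimate about 5.3 of 6, power 64-72% (71-79% with the same losses at random). At 9.3, power is 95-98%.

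**5. A cruder bound.** Suppose exits are exactly the worst-changing fraction q of each arm. The mean of those who remain then shifts by SD × φ(z) / (1 - q), where z is the 1 - q normal quantile. With SD 7.4 the shift is 1.44 at q = 10% and 0.80 at q = 5%, so exits of 10% vs 5% shrink the difference by 0.64. Exits of 20% vs 10% shrink it by 1.15. The simulated bias is smaller because the rule acts on a noisy, earlier BDI. Equal exit rates give no bias in this model, and more exits on fish oil would reverse its direction.

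**6. Modelling from the recorded scores.** Sequential regression on the recorded BDI and MADRS returns 5.94-6.07, with a standard error 1-8% larger than under full follow-up.

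**The case against.** The strongest reply is that the consequence is small and the remedy gains little.

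- **Bias against noise.** The bias is 0.26 to 0.62 points against a standard error of 7.8 × √(2/30) = 2.0, or 0.13 to 0.31 standard errors. Power at the planned effect is barely touched. This stands.
- **The fix does not clearly beat the present design.** If capsule benefit stops accruing at exit and rescue care adds 0-5 points (assumed), an as-assigned week-12 comparison shows 5.0-6.0 of a true 6, with power 71-82%. Modelling the data already collected gives 5.9-6.1. This stands for BDI exits, where the trigger is itself a recorded score. It is untested for item-9 and antidepressant-change exits, which were not simulated. Antidepressant changes have no score trigger, so recorded scores may explain them less well.
- **A depression score exists at exit.** BDI and item-9 exits carry a BDI by construction, and the BDI is an Aim 1 measure. That is true, but the MADRS is the primary outcome.
- **Stopping is a reasoned choice.** The protocol cites the short study duration, and the question concerns fish oil on stable antidepressants. Scores after rescue care answer a different question. That is fair, but collecting them does not prevent an analysis that sets them aside, whereas not collecting them closes off the alternative.
- **The exit mix is unknown.** MS exacerbation and changes of disease-modifying drug also end participation, and an antidepressant change need not mean worsening. This stands and limits the claim to some subjects.
- **The simulated contacts follow Table 1.** Fortnightly monitoring after month 1, as Protection against risk requires, implies a week-6 contact that Table 1 lacks. Adding it changes the results little.

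**Conclusion.** The concern holds. The protocol ends data collection for subjects who worsen, and those exited before week 12 lose the primary outcome. Those exited in the first three weeks have no post-baseline MADRS.

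The harm is modest. Under the assumed settings with a true difference of 6, a comparison of subjects with a week-12 score understates the effect by about 0.3 to 0.6 points, with power of 70-81% instead of 83%. There is no false-positive risk and no material loss of power at 9.3 units. Otherwise the trial must rely on a model where data could have been collected.

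All exit rates are assumed, and the item-9 and antidepressant-change routes carry no number. It should be fixed because the loss is avoidable and only protocol wording can prevent it. Confidence is medium.

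**What to change.** Keep the referral and every safety rule. In Visit 4, the closing paragraph of the Exclusion Criteria, and Protection against risk, replace the wording that ends study participation with:

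*Study capsules are stopped. A MADRS and BDI are obtained at that contact or as soon as possible, without delaying care, noting the date and any change of care already made. The scheduled MADRS and BDI through week 12 continue unless consent is withdrawn.*

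Record the exit MADRS separately, as the last value before care changes.

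The cost is protocol and consent wording plus about 3 to 31 extra MADRS interviews over the whole trial at baseline means of 18-22. These are the exit ratings at weeks 1, 2, 3 or 10 and the remaining week-4, 8 and 12 ratings.

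There are two downsides. The MADRS is an interview, so an exit found by phone may be rated after care has begun. Later scores will also reflect any rescue care. The change removes avoidable missing data. It does not promise to restore full power or to estimate the on-treatment effect.

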#### Visit 6 (week 8)

MADRS and BDI will be administered. A research assistant will assess the subject for adverse events and perform a pill count. The subject will also be asked about any changes in medication

or doses of medications (prescribed and over the counter). The subject will be instructed to bring their medication bottle to their next scheduled visit.

Visit 7 (week 12)

This visit will assess all of the same measures as Visit 2. In addition, the subject will return all remaining study drug and a pill count will be performed. If the subject has achieved a 50% improvement on their BDI or MADRS score they may choose to continue on in the study for another 3 months or to exit the study. If the subject chooses to remain in the study, we will review the consent form for Phase II of the study and attain consent before proceeding with Phase II. After being consented the subject for the subject will receive another month’s supply of study medication and will be instructed to bring this bottle to their next scheduled visit.

Table 1. Study Schedule: Phase I

| **Assessments** | **Visit 1**  Screen | **Visit 2**  Baseline | **Visit 3**  Wk 0 | Phone  Wk 1 | **Visit 4**  Wk 2 | Phone  Wk 3 | **Visit 5**  Wk 4 | **Visit 6**  Wk 8 | Phone  Wk 10 | **Visit 7**  Wk 12 |
| --- | --- | --- | --- | --- | --- | --- | --- | --- | --- | --- |
| Family and Medical Hx | X |  |  |  |  |  |  |  |  |  |
| PE/Neurological exam/EDSS |  | X |  |  |  |  |  |  |  | X |
| SCID | X |  |  |  |  |  |  |  |  |  |
| BDI | X | X |  | X | X | X | X | X | X | X |
| MADRS | X | X |  |  |  |  | X | X |  | X |
| MMSE | X |  |  |  |  |  |  |  |  |  |
| MSQLI |  | X |  |  |  |  | X |  |  | X |
| MSFC |  | X |  |  |  |  |  |  |  | X |
| Cytokine measurement |  | X |  |  |  |  | X |  |  | X |
| Metabolic panel, PT time |  | X |  |  |  |  | X |  |  | X |
| RBC fatty acid |  | X |  |  |  |  | X |  |  | X |
| Food freq. survey |  | X |  |  |  |  |  |  |  | X |
| Concomitant medications | X | X |  |  |  |  | X | X |  | X |
| Adverse Events |  |  | X | X | X | X | X | X | X | X |
| Pill Count |  |  |  |  |  |  | X | X |  | X |
| Blinding evaluation |  |  |  |  |  |  |  |  |  | X |

Table 2. Study Schedule: Phase II

| **Assessments** | Month 4 | | Month 5 | | Month 6 | |
| --- | --- | --- | --- | --- | --- | --- |
| Phone  wk  14 | Visit 8 wk  16 | phone  wk  18 | Visit 9 wk  20 | phone  wk  22 | Visit 10 wk  24 |
| Family and Medical History |  |  |  |  |  |  |
| PE/Neurological exam/EDSS |  |  |  |  |  | X |
| SCID |  |  |  |  |  | X |
| MADRS |  | X |  | X |  | X |
| BDI | X | X | X | X | X | X |
| MSQLI |  |  |  |  |  | X |
| MSFC |  |  |  |  |  | X |
| Cytokine measurement |  |  |  |  |  | X |
| Metabolic panel, PT |  |  |  |  |  | X |
| RBC fatty acid |  |  |  |  |  | X |
| Food freq. survey |  |  |  |  |  | X |
| Concomitant medications |  | X |  | X |  | X |
| Adverse Events | X | X | X | X | X | X |
| Pill Count |  | X |  | X |  | X |
| Blinding evaluation |  |  |  |  |  | X |

#### Phase II: Visits 8(week 16) and Visit 9 (week 20)

Subjects will be come into the clinic to be assessed for MADRS and BDI. A research assistant will assess the subject for adverse events and perform a pill count. The subject will also be asked about any changes in medication or doses of medications (prescribed and over the counter). (**See Table 2: Study Schedule: Phase II**)

Phase II: Visit 10 (week 24)

The subject will be re-screened for MDD using the SCID and attain a MADRS score. [name] will perform a brief PE and a neurological exam (EDSS). A research assistant will administer the MSFC and record concomitant medications. The subject will fill out study questionnaires, which include: BDI, MSQLI, Food Frequency. A research assistant will draw blood for comprehensive metabolic function, PT/INR, cytokine levels, and RBC fatty acid analysis. Adverse events, pill count, and concomitant medications will be recorded at this visit. A short questionnaire that assesses subject blinding will be administered at this visit.

#### Study dose

We are using doses and ratios of EPA and DHA similar to those reported to improve depression in people on stable doses of antidepressant medication [6]. The subjects randomized to the fish oil group will receive 6.0 grams of fish oil per day providing 2.1 g/day of EPA and 1.5g/day of DHA. Subjects will take 3 capsules twice a day with meals. The placebo capsules will contain soybean oil with 1% fish oil so that it will be flavored to taste and smell similar to the fish oil capsules. The placebo group will receive 6 placebo capsules per day and will take 3 capsules twice a day with meals.

